### Hypotheses

 1. Aldosterone antagonism with eplerenone in diabetic cardiomyopathy leads to an improvement in LV systolic and diastolic function, measured by 2D speckle tracking strain and strain rate imaging.

 2. Myocardial fibrosis, as measured by echocardiographic calibrated IB and serum collagen biomarkers is reduced by eplerenone.

 3. Eplerenone improves LA function and phasic volumes.

 4. Changes in LV and LA function with eplerenone are correlated with changes in the degree of myocardial fibrosis.

### Statistical considerations

#### Sample size determination

At the time of study design and commencement, there were no studies that examined the impact of aldosterone antagonism with eplerenone on cardiac function as measured by strain and strain rate imaging and cardiac fibrosis in patients with diabetic cardiomyopathy. Therefore, sample size calculation was based on previous studies that examined the effects of spironolactone on strain and strain rate in patients with diastolic heart failure from dilated and hypertensive cardiomyopathies, changes in myocardial calibrated IB in these patients, as well as differences in IB between patients with early diabetic cardiomyopathy and normal controls [12,13,28,31]. The change in IB between baseline and 12 month echocardiograms will be measured in both placebo and eplerenone arms (ΔIB). A sample size of 65 patients per treatment group (130 patients in total) will achieve 80% power to detect a difference in ΔIB of −4.5 dB (SD = 7) with two-sided α = 0.05 using a two-sample t-test. This includes a 10% loss to follow-up rate for clinic visits and repeat echocardiograms, as well as a 15% non-compliance rate with eplerenone or placebo. A power of at least 80% was also obtained for peak longitudinal systolic strain and strain rate, and early diastolic strain rate using similar calculations.

Since commencement of this study, Kosmala and colleagues [14] examined the effects of spironolactone versus placebo on cardiac function in patients with metabolic syndrome and found improvements in longitudinal strain and strain rate over a 6-month period, but no significant difference in ΔIB. Sample size recalculation has shown that the intended sample size of 130 patients in the present study provides adequate power to detect a difference over the 12 month time period in LV strain and strain rate.

These sample size calculations are based on a two-sample t-test and are therefore conservative. As analysis of covariance (ANCOVA) adjusted for the baseline measurement will be the method of analysis, the power will be higher or the minimal detectable effect smaller for the same power target. The gain in efficiency is linked to the correlation (r) between the baseline and on-treatment measurements which is currently unknown for the endpoints involved, but expected to be high [32].

#### Trial oversight

A data safety and monitoring board (DSMB) comprising of personnel with sufficient cardiological, endocrinological and statistical experience will be formed to review the interim results and oversee the conduct of the trial. The DSMB and ethics committee will review all unblinded data on clinical endpoint events and determine whether events meet pre-specified criteria. The DSMB will monitor safety and efficacy of the trial and periodically assess whether the trial should continue.

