### Research design and methods

This study was designed as a prospective, investigator-initiated, multi-centre, randomized, double blind, placebo controlled study to evaluate the impact of treatment with eplerenone for 12 months on myocardial structure and function in patients with T2DM and LV diastolic or systolic dysfunction, in the absence of class III-IV symptoms with severe LV systolic dysfunction. The study was conducted in accordance with the NHMRC guidelines and was approved by Sydney Southwest Area Health Service Human Research Ethics committee. Figure 2 shows the study design and protocol.

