### Endpoints

The primary endpoints are changes in global mean peak LV systolic strain and strain rate, peak early diastolic myocardial tissue Doppler velocities at the basal septal LV wall (e’), the ratio of mitral inflow early diastolic velocity to peak early diastolic mitral annular velocity (E/e’), LV calibrated IB, LV mass index and LA strain and strain rate at ventricular systole and early and late ventricular diastole, and LA phasic volumes. Secondary endpoints include changes in collagen turnover measured as changes in serum levels of procollagen type I aminoterminal peptide (PINP), PIIINP, PICP, matrix metalloproteinases 1 and 9 (MMP-1, MMP-9), tissue inhibitor of metalloproteinase-1 (TIMP-1), renin, and aldosterone levels). Other secondary endpoint measurements include MRC dyspnea score, exercise tolerance, as measured by 6-minute walk test distance and incidence of atrial fibrillation.

Serious adverse events (SAE) including life-threatening hyperkalemia (>7mmol/L), acute renal failure, hypotension and death will be monitored.

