#### Statistical analysis

The intention-to-treat principle will be applied to the analysis. Baseline and demographic characteristics will also be summarized by treatment group. All changes from baseline, including the primary and secondary end-points will be analysed by means of ANCOVA, adjusted for the baseline measurement.

Descriptive statistics will be provided for safety data. The number of patients reporting any SAE, the occurrence of specific SAEs and discontinuation due to SAEs will be tabulated. The effect of treatment on the number of patients experiencing at least one SAE will be tested using a χ^2^-test or Fisher’s exact test if the number of events is small. All hypotheses are two-sided. A p-value of <0.05 is considered statistically significant.

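### Clinical endpoint events are to be classified by bodies that know the allocation, which exposes atrial fibrillation incidence and possibly the SAE comparison

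*Protocol article*

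**What the plan says.** Research design and methods describes a "randomized, double blind, placebo controlled study to evaluate the impact of treatment with eplerenone for 12 months".

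Trial oversight then states: "The DSMB and ethics committee will review all unblinded data on clinical endpoint events and determine whether events meet pre-specified criteria". The next sentence gives the DSMB a second job: "The DSMB will monitor safety and efficacy of the trial and periodically assess whether the trial should continue". Interim analysis sets early-termination thresholds of two-sided p<0.003 for benefit and p<0.01 for harm.

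Two kinds of clinical event appear in the comparisons:

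- Endpoints ends its list of secondary measures with "exercise tolerance, as measured by 6-minute walk test distance and incidence of atrial fibrillation".
- Endpoints also says, in a separate paragraph: "Serious adverse events (SAE) including life-threatening hyperkalemia (>7mmol/L), acute renal failure, hypotension and death will be monitored". Under Statistical analysis, "The effect of treatment on the number of patients experiencing at least one SAE will be tested using a χ^2^-test or Fisher’s exact test", at a two-sided 0.05 level.

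The article describes no other step at which events are classified, blinded or not.

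**The concern.** Deciding whether an event meets set criteria is adjudication. When the people deciding know the treatment arm, a borderline case can be accepted in one arm and rejected in the other, and nothing in the final data would show it. The risk is sharper here because expectations about the drug are strong: the Background raises hyperkalemia with aldosterone antagonists in type 2 diabetes as a worry, and says the study will supply safety information on that question. A classifier who knows the arm therefore has a prior view of which patients should have potassium or renal events.

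The roles are also merged. The DSMB would decide which events count and then advise on continuing the trial from results that may include them.

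At stake is the credibility of the atrial fibrillation result and, depending on how the SAE count is formed, of the SAE comparison. The direction of any bias could not be recovered afterwards.

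**Working it through.** No figure in the article is in dispute, so the main check sets the sections side by side.

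**1. What loses the blind.** The sentence in Trial oversight covers review of unblinded data and the decision on whether events qualify. It says nothing about how sites or patients detect and report events, and the design keeps those blinded. Only classification is done with allocation known.

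**2. Which results pass through that step.**

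| Result | Exposed? | Reason |
|---|---|---|
| Primary endpoints (strain, e', E/e', calibrated IB, LV mass index, LA measures) | No | Echocardiographic measurements, not classified events |
| Collagen markers, renin, aldosterone | No | Laboratory values |
| MRC dyspnea score, 6-minute walk | No | Functional measures, not classified events |
| Atrial fibrillation incidence | Yes | A clinical event and a secondary endpoint |
| SAE: death, potassium >7 mmol/L | Little | Little room for judgement |
| SAE: acute renal failure, hypotension | Yes, if this step feeds the SAE count | The article gives no numerical threshold for either |

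**3. How sensitive a small-count test is.** Inputs: 65 per arm (Sample size determination); two-sided 0.05 and Fisher's exact test for small numbers (Statistical analysis). The event counts are assumed. With all events in one of two equal arms, the two-sided Fisher p-value for k v 0 is 2 × C(65,k) / C(130,k).

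- k=5: 2 × (65·64·63·62·61)/(130·129·128·127·126) = 2 × 0.02886 = 0.0577.
- k=6: 2 × 0.02886 × (60/125) = 2 × 0.01385 = 0.0277.

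Dropping one of six events therefore moves the result from one side of 0.05 to the other.

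**4. What one-sided classification could do to the error rate.** Assume 65 per arm, the same true event rate p in both arms, and a share d of events rejected in one arm only. The chance of a false positive is the sum, over all counts a and b, of Bin(a; 65, p) × Bin(b; 65, p(1−d)) for pairs where the uncorrected χ² exceeds 3.84.

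| True rate p | d=0 | d=10% | d=20% | d=30% |
|---|---|---|---|---|
| 10% | 5.1% | 5.5% | 6.9% | 9.4% |
| 20% | 4.9% | 5.8% | 8.8% | 14.4% |
| 30% | 5.2% | 6.9% | 12.3% | 22.2% |

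Both p and d are assumptions, because the article gives neither.

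**The case against.** Several points on the other side are sound.

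- **A DSMB that sees unblinded data is normal and compatible with a double-blind trial.** This stands. A reader might infer that Trial oversight contradicts the double-blind label, or that event ascertainment as a whole is unblinded. The article supports neither. The fault is only that unblinded bodies also decide which events count.
- **The route to the SAE test is not stated.** This stands too. Trial oversight speaks of clinical endpoint events, while Endpoints lists SAEs in a separate paragraph as events to be monitored. Statistical analysis counts patients reporting an SAE and does not say that only accepted events enter. The SAE test is therefore exposed conditionally; atrial fibrillation is the clearer case.
- **The pre-specified criteria might be monitoring or stopping criteria.** The sentence does sit between the interim review and the decision to continue. But it asks whether events meet the criteria, which is the language of classification. If another meaning was intended, the wording still needs changing.
- **A condensed article leaves division of work to a charter.** That would answer a complaint about missing detail. Here the article states a rule, and the rule is the problem.
- **The Fisher figures do not measure bias.** Correct. A test on few events is fragile under blinded classification as well, and the counts were chosen to straddle 0.05. They show only why a single decision can matter.

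**Conclusion.** The point holds in a limited form. As written, the article assigns event classification to the DSMB and the ethics committee from unblinded data, and the DSMB also advises on stopping. Atrial fibrillation incidence is exposed. The SAE comparison is exposed only if the same classification decides which SAEs are counted, and then mainly for acute renal failure and hypotension.

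A reader might infer that the trial's main results are at risk. They are not: no primary endpoint passes through this step, and neither do the biomarkers.

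The size of any bias is unknown. Under the assumptions shown, rejecting 10% to 30% of events in one arm only would put the false-positive rate between about 5.5% and 22%, depending on the event rate. These figures show what differential classification could do; they are no evidence that it would occur. The verdict rests on reading the sentence in Trial oversight as event classification, which is its plain sense.

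**What to change.** Reword the sentence in Trial oversight so that:

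1. trial personnel blinded to allocation classify each clinical endpoint event against the pre-specified criteria; site investigators, who are blinded under the double-blind design, could do this;
2. the classification is locked before anyone reviews events by arm;
3. the DSMB then reviews the classified events by arm for monitoring only;
4. the ethics committee has no role in classifying events from unblinded data.

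The same passage should say whether this classification decides which events enter the SAE count.

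The cost is a change of wording in the oversight section and the DSMB charter, plus a small amount of added work for the blinded investigators. The article does not say that investigators already review these events, so that work should be counted as new. A separate committee is not required.

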#### Interim analysis

Interim analyses for safety and efficacy are incorporated into this trial. The Haybittle-Peto rule with two interim efficacy analyses detailed in a statistical analysis plan are planned after approximately 30% and 60% of the patients have been followed up at 12 months. Early termination for the study will be recommended for evidence of overwhelming benefit (2-sided p < 0.003 favouring eplerenone) or substantive harm (2-sided p < 0.01 against eplerenone).

#### Statistical analysis

The intention-to-treat principle will be applied to the analysis. Baseline and demographic characteristics will also be summarized by treatment group. All changes from baseline, including the primary and secondary end-points will be analysed by means of ANCOVA, adjusted for the baseline measurement.

Descriptive statistics will be provided for safety data. The number of patients reporting any SAE, the occurrence of specific SAEs and discontinuation due to SAEs will be tabulated. The effect of treatment on the number of patients experiencing at least one SAE will be tested using a χ^2^-test or Fisher’s exact test if the number of events is small. All hypotheses are two-sided. A p-value of <0.05 is considered statistically significant.

## Discussion

There are features of this trial design that deserve particular emphasis:

● Patients of all symptomatology and degrees of myocardial abnormalities ranging from grade 1–3 diastolic dysfunction to mild to moderate systolic dysfunction are enrolled. Including patients with more severe grades of baseline diastolic or systolic dysfunction may allow greater improvement on eplerenone. Furthermore, patients with milder degrees of systolic/diastolic dysfunction randomized to placebo may experience disease progression during the course of the study.

● Blood pressure independent effects of eplerenone will be examined by recruiting those with stable blood pressure control at baseline, and blood pressure will be continually monitored to ensure stability throughout the study. Furthermore, the dose of eplerenone will not exceed 50mg daily, minimizing the antihypertensive effects.

● The impact of aldosterone antagonism on myocardial fibrosis will be measured both by cardiac imaging and serum levels of biomarkers. Furthermore, attempts will be made to correlate the changes in myocardial function with changes in the degree of myocardial fibrosis both on imaging as well as changes in biomarker levels.

● In comparison to previous studies examining biomarkers of fibrosis, it is assumed that the beneficial effects of aldosterone antagonism come from more effective suppression of aldosterone, yet few have definitively shown that this beneficial effect is present despite a persistently elevated renin and aldosterone level after treatment. We will measure both renin and aldosterone level before and after treatment in our study.

## Summary

Diabetic cardiomyopathy is an increasingly prevalent disorder for which there is currently no specific therapeutic intervention. This trial, when successfully completed, will advance our understanding of diabetic cardiomyopathy and the underlying mechanisms. This may provide a new direction in the management of diabetes; the early treatment by eplerenone may prevent and reverse the progression of atrial and ventricular dysfunction and myocardial fibrosis to irreversible structural and symptomatic cardiac disease. Thus, the proposed research will have a favourable impact in turning the focus of treatment of this disease from secondary prevention and heart failure symptom management into an interventional approach at the preclinical stage. This may result in a reduction in morbidity and mortality for patients with T2DM, with improved outcomes and consequent substantial health cost savings for the community.

## Abbreviations

2D: 2-dimensional; ACEI: Angiotensin converting enzyme inhibitors; AMI: Acute myocardial infarction; ARB: Angiotensin receptor blockers; CAD: Coronary artery disease; IB: Integrated backscatter; DSMB: Data safety and monitoring board; e’: Peak early diastolic velocity; E/e’: Ratio of mitral inflow early diastolic velocity to peak early diastolic mitral annular velocity; HbA1c: Glycosylated hemoglobin A1c; LA: Left atrial; LV: Left ventricular; MMPs: Matrix metalloproteinases; MMP-1: Matrix metalloproteinase 1; MMP-9: Matrix metalloproteinase 9; NYHA: New York Heart Association functional class; PICP: Procollagen type I carboxy-terminal propeptide; PIIINP: Procollagen type III amino-terminal propeptide; PINP: Procollagen type I aminoterminal peptide; RAAS: Renin angiotension-II aldosterone system; TGF-β: Transforming growth factor-β; TIMP-1: Tissue inhibitor of metalloproteinase 1; T2DM: Type 2 diabetes mellitus.
